|                                            | 
SAEs and AESIs will be actively monitored for about 365 days after the study vaccination.
 
IDMC: An Independent Data Monitoring Committee (IDMC) will be set up to review the safety data after the study vaccination,
 
Participants can choose whether to be blinded or not after obtaining statistically significant vaccine efficacy and adequate safety data. Participants will be encouraged to remain in the ongoing study until the end of the study, unless they request to withdraw from the study for any reason. SAEs and AESIs would be monitored during this time.
 
For participants who request to be unblinded and are confirmed to be placebo recipients, the following procedure is available:
 
 
1) remain in the study for continued follow-up;
 
2) withdraw from the study by vaccination with other marketed vaccines;
 
3) withdraw from the study for other reasons.
 
 
Participants who receive or request any other COVID-19 vaccination during the study should withdraw from the study.
 |
| 
Total Number of Participants
 | 
Approximately 10,000 participants are planned to be enrolled. The percentage of participants aged <math>\geq 60</math> years shouldn't be less than 20%, and the percentage of participants who have received 3 doses of inactive COVID-19 vaccines shouldn't be less than 60%. The exact number of participants enrolled in the study will depend on the infection rate of COVID-19 at the time of the enrollment and the true VE (vaccine efficacy) of SCTV01E. If the attack rate is much higher, case accrual would be expected to be more rapid, enabling the study's primary endpoint to be evaluated much sooner and the actual enrolled sample size may be less than planned.
                                                                                                                                                                                                                                                                                                                                                                                                                         |

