**Safety Analysis**

Safety analysis will be based on SS.

AEs and SAEs are encoded based on the *Medical Dictionary for Regulatory Activities* (MedDRA), and also based document the classified statistics were made according to the system organ class (SOC) and preferred term (PT). In this trial, the solicited adverse events (both systemic and local ) will be summarized and classified according to PT.

In this trial, the treatment emergent adverse events (TEAEs) will be summarized, and the adverse medical conditions occurring before the study vaccination are listed. Unless otherwise specified, the adverse events as described below are TEAEs.

The number of occurrences, number of cases and incidence rate of AEs, SAEs and AESIs in each group will be summarized respectively. The adverse events related to the study vaccine, SAEs and AESIs will be listed.

Supplemental analysis will be performed on adverse events in the following populations:

- Participants who have negative results of PCR test at baseline and negative results of rapid antigen test on Day 7;
- Participants who have negative results of PCR test at baseline and negative results or absence of rapid antigen test on Day 7;

- Participants who have positive results of PCR test at baseline.

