**Immunogenicity evaluation:** Blood samples will be collected on Day 0 (pre-vaccination), Day 14 and Day 28 from participants in the immunogenicity subgroup (approximately 5%–10% of randomized participants), of which 200 participants need to undergo additional scheduled sampling on Day 7, Day 90 and other longer periods (detailed in the visit flow chart of the protocol) for the detection of SARS-CoV-2 (including mutant strains and mutant subtype) neutralizing antibody.

**Safety evaluation:** All participants will be observed at the study site for at least 30 minutes after the study intervention. Information is collected through a combination of active surveillance and spontaneous reporting. Solicited adverse events (AEs) within 7 days after vaccination and unsolicited AEs within 28 days after vaccination will be collected via vaccination record cards (VRCs). Serious adverse events (SAEs) and adverse events of special interest (AESIs) will be collected through active surveillance until the participant completes (or withdraws early from) the study.

This study will be conducted by Guizhou Center for Disease Control and Prevention, Sichuan Center for Disease Control and Prevention, and Hunan Provincial Center for Disease Control and Prevention.

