#### **7.7.2 SAEs**

The number of participants and incidence of SAEs in each group are calculated as follows:

- All SAEs;
- SAEs related to the study vaccine;
- SAEs related to the study vaccine with severity  $\geq$  Grade 3;

A list of SAEs is provided.

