#### **7.7.3 AESIs**

The number of participants and incidence of AESIs in each group are calculated as follows:

- All AESIs;
- AESIs related to the study vaccine;

A list of AESIs is provided.

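### Late SAE and AESI percentages could be distorted if withdrawal for another COVID-19 vaccine differs by arm, because SAP 7.7.2 and 7.7.3 use neither person-time nor a cut at unblinding

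*Combined protocol and SAP*

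**What the plan says.** **Length of follow-up.** The protocol synopsis (Study Design) states: "SAEs and AESIs will be actively monitored for about 365 days after the study vaccination". SAP 4.1 ends collection earlier for those who leave: these events "will be collected through active surveillance until the participant completes (or withdraws early from) the study".

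**Who leaves.** The synopsis states: "Participants can choose whether to be blinded or not after obtaining statistically significant vaccine efficacy and adequate safety data". Among the options for participants who ask to be unblinded and prove to be on placebo is to "withdraw from the study by vaccination with other marketed vaccines"; note 9 to Table 1 repeats this list. The general rule covers both arms: "Participants who receive or request any other COVID-19 vaccination during the study should withdraw from the study". The Table 1 note on visits V8 and V9 says the same of those who received another vaccine.

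**How events are summarised.** SAP 7.7.2: "The number of participants and incidence of SAEs in each group are calculated as follows". SAP 7.7.3: "The number of participants and incidence of AESIs in each group are calculated as follows". The synopsis (Safety Analysis) has: "The number of occurrences, number of cases and incidence rate of AEs, SAEs and AESIs in each group will be summarized respectively". It mentions an incidence rate, but neither document defines person-time, a censoring rule or a cut at unblinding for safety. SAP 7.8 leaves missing safety data unhandled. For efficacy, by contrast, SAP 7.6.1 uses person-years at risk and censors at another COVID-19 vaccination.

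**Two statements that do not fit.** SAP 7.1.2 limits the analysed adverse events to 28 days and lists later ones separately, while the monitoring period for SAEs and AESIs is about a year. The synopsis (Interim and final analysis) and SAP 7.11 say that participants stay blinded during long-term follow-up, while the synopsis (Study Design) and visit V8 of Table 1 offer a choice of unblinding.

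**The concern.** An event can be counted only while a participant is under observation. The exit to a marketed vaccine is spelled out for unblinded placebo recipients, so placebo follow-up may end earlier on average. A percentage of all participants in the arm treats someone followed for 120 days like someone followed for 365. If placebo time is shorter, the placebo percentage is too low and the vaccine looks less safe by comparison. Late events in those who left are not seen at all. At stake is the reading of SAEs and AESIs after unblinding. Solicited events (Day 0 to 7) and unsolicited events (Day 0 to 28) fall before almost any unblinding that follows the final analysis.

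**Working it through.** The plan states no figure for long-term safety, so there is none to reproduce. The steps below check whether late events matter in the tables, how early unblinding could come, and how large the distortion could be.

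**1. Late SAEs are tabulated by arm.** Table S6 (supplementary appendix) gives n and % of N. Pooling its two baseline strata:

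- Placebo: 32 + 6 = 38 of 3879 + 716 = 4595, or 0.83%. Within 28 days 13 + 4 = 17; later 19 + 2 = 21.
- SCTV01E: 36 + 4 = 40 of 3967 + 634 = 4601, or 0.87%. Within 28 days 19 + 1 = 20; later 17 + 3 = 20.

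About half of the participants with an SAE (21 of 38 and 20 of 40) fall in the later row. AESIs are zero in both arms.

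**2. Unblinding could come well before Day 365.** From the sample size section: 5,000 per arm × 0.85 × 0.90 = 3,825. At 1.5% per month on placebo and VE 70%, monthly cases are 3,825 × 0.015 × (1 + 0.3) = 75, so 59 cases need 59 / 75 = 0.8 months at risk. With the per-protocol efficacy set in Table S2 (1309 and 1314): 1309 × 0.015 + 1314 × 0.015 × 0.3 = 25.5 per month, or 59 / 25.5 = 2.3 months. Enrolment, database lock and review add to this. An assumed exit day between 90 and 240 is therefore plausible, but the documents do not fix it.

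**3. Size under assumed exit.** Assume the same constant event rate in both arms and a fraction w leaving at day U. Mean follow-up is (1 − w) × 365 + w × U. For rare events the crude vaccine/placebo ratio is close to the ratio of mean follow-up.

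| Leave placebo / vaccine | Day U | Mean days placebo | Mean days vaccine | Crude ratio |
|---|---|---|---|---|
| 10% / 0% | 240 | 352.5 | 365 | 1.035 |
| 10% / 0% | 90 | 337.5 | 365 | 1.081 |
| 20% / 0% | 180 | 328 | 365 | 1.113 |
| 25% / 5% | 90 | 296.25 | 351.25 | 1.186 |
| 50% / 5% | 90 | 227.5 | 351.25 | 1.544 |
| 50% / 50% | any | equal | equal | 1.000 |

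An exact constant-hazard calculation with one-year SAE risks of 1%, 2% and 5% gives nearly the same ratios. The ratio of events per person-year is 1.00 in every row.

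**4. Scale.** The only planned figure is about 10% dropout overall. With 1:1 allocation, 20% of placebo and nobody on vaccine already uses all of it. In that row placebo loses 1 − 328/365 = 10% of its follow-up, or about 4 of every 40 events.

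**The case against.** The strongest reply is that the plan makes no formal claim here. Safety P values are nominal (SAP 7.10), and SAP 7.7 plans counts and percentages without a test. The withdrawal rule covers both arms, unblinding is by request, and participants are encouraged to stay. SAP 7.2 analyses the reasons for early withdrawal, so unequal leaving should be visible. Those who withdraw because of an adverse event are still followed to outcome. The distortion in the milder rows is also small against chance. From Table S6 the crude SAE ratio is 0.87 / 0.83 = 1.05; with a log standard error of √(1/40 + 1/38) = 0.227, the approximate 95% interval is 0.67 to 1.64.

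Most of this stands and limits the point. It does not remove it: a descriptive table can still mislead, and reasons for withdrawal do not supply a time denominator.

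A reader might infer more than the documents support:

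- *That the comparison will be distorted.* This needs unequal withdrawal, and no rate by arm is given. That vaccine recipients have less reason to leave is plausible but is inference.
- *That a 365-day between-group comparison is a stated endpoint.* The endpoint is the incidence and severity of SAEs and AESIs, without a window. The 365 days are a monitoring period.
- *That the distortion is large.* If 60% of placebo and nobody on vaccine left at Day 90, the ratio would be 365 / 200 = 1.82, but nothing in the documents supports such an exit.
- *That Table S6 already shows the bias.* Later SAEs are 21 of 4595 and 20 of 4601, with no visible imbalance. The table does not say whether it includes time after unblinding.

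**Conclusion.** The point holds in a limited form. SAE and AESI collection stops at withdrawal, an exit is listed for unblinded placebo recipients, and the safety summaries have no person-time and no cut at unblinding. Late SAE and AESI percentages could therefore be distorted if withdrawal differs by arm. Results to Day 28 are largely unaffected, except possibly for the last participants enrolled.

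Under equal true rates and placebo-only exit, the crude ratio is 1.035 to 1.08 for 10% leaving and 1.11 for 20% leaving at Day 180. It is larger only with heavier assumed exit, and 1.00 if leaving is equal. These are illustrations; the documents give neither withdrawal by arm nor the day of unblinding. If more placebo recipients leave, the error runs against the vaccine. Whether the mechanism operates at all depends on the unresolved conflict over blinding. This is a change worth making, but it does not threaten the primary result.

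**What to change.** In SAP 7.7.2 and 7.7.3:

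1. State the SAE and AESI analysis window, and reconcile the 28-day rule in SAP 7.1.2 with the monitoring period in the synopsis and SAP 4.1.
2. Report events per person-year by arm, with time ending at withdrawal or other COVID-19 vaccination, whichever is earlier. SAP 7.6.1 already censors efficacy time at other vaccination.
3. Give follow-up time and the number and timing of withdrawals by arm.
4. Make the blinded period the main between-group summary, and show events after unblinding separately.

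Reconcile the synopsis (Study Design) and visit V8 with the synopsis (Interim and final analysis) and SAP 7.11 on whether participants remain blinded.

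The cost is about one table, using data already collected. Person-year rates correct for unequal follow-up but do not remove bias from informative withdrawal; the blinded-period summary and the withdrawals by arm help the reader judge that. Safety contact after withdrawal is not part of this request. The Table 1 note on V8 and V9 withdraws those who received another vaccine, so such contact would need a protocol change and consent.

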**Withdrawal determined by the investigator:**

Withdrawal from the study means that the investigator may determine that the enrolled participant should withdraw from the study when he or she is not suitable for continuing the study during the trial, for the following reasons:

- 1) Participants developed intolerable AE, and the investigator determined that continuing the study would be detrimental to the participant's health;
- 2) Major protocol deviation that may affect the safety of the participant;
- 3) Other reasons that disqualify participants from continuing this study as determined by the investigator.

**Handling participants withdrawing:**

Investigators should try their best to get in touch with participants who have not been to the site for regular follow-up. Investigators will follow up with participants who withdraw from the study due to serious adverse events or adverse events until the adverse events disappear, ease, stabilize, or other outcomes. If a participant withdraws from the study, the nasal/nasopharyngeal/throat swab and blood samples collected before the withdrawal date can still be used for study analysis, unless the participant specifically requests otherwise.

The investigator should record relevant information about withdrawal from the study in the electronic case report form (eCRF), including whether the participant or the investigator made the withdrawal decision, and a detailed record of the specific circumstances:

- 1) Losing contact;
- 2) Death, the investigator should record the cause of death;

|                                              |                                                                                                                                                                                                                                                                                                                                                                                                                                                                                                                                                                                                                                                                                                                                                                                                                                                                                                                                                                                                                                                                                                                                                                                                                    |
|----------------------------------------------|--------------------------------------------------------------------------------------------------------------------------------------------------------------------------------------------------------------------------------------------------------------------------------------------------------------------------------------------------------------------------------------------------------------------------------------------------------------------------------------------------------------------------------------------------------------------------------------------------------------------------------------------------------------------------------------------------------------------------------------------------------------------------------------------------------------------------------------------------------------------------------------------------------------------------------------------------------------------------------------------------------------------------------------------------------------------------------------------------------------------------------------------------------------------------------------------------------------------|
|                                              | 
3) For voluntary withdrawal, the investigator should record the withdrawal and reason;
 
 
• Participants voluntarily withdraw from all studies, including all study activities such as vaccination, biological sample collection and safety observation;
 
• Participants voluntarily withdraw from part of the study, such as only stopping vaccination or only stopping biological sample collection, etc., other studies specified in the plan should continue to be completed;
 
• Participants request to withdraw due to study-related reasons, such as intolerance of adverse events, etc.;
 
• Participants request to withdraw due to reasons unrelated to the study, such as long-term outings, relocation, etc.;
 
 
4) It is determined by investigators that the participant should withdraw from the study;
 
5) Other reasons.
 
If a participant withdraws from the study or terminates the study (including loss to follow-up) after enrollment, no participant replacement is allowed.
 
After unblinding, participants who still choose to stay in the study will continue their safety follow-up.
 |
| Study Suspension/Termination Criteria | 
In one of the following situations, the trial should be suspended or terminated:
 
 
• When the IDMC requires a suspension/complete termination of the trial and the sponsor agrees;
 
• When the sponsor requires a suspension/complete termination of the trial and gives reasons for it;
 
• When the Ethics Committee requires a suspension/complete termination of the trial and gives reasons for it;
 
                                                                                                                                                                                                                                                                                                                                                                                                                                                                                                                                                                                                                                                                                                                              |

|                             |                                                                                                                                                                                                                                                                                                                                                                                                                                                                                                                                                                                                                                                                                                                                                                                                                                                                                                                                                                                                                                                                                                                                                                               |
|-----------------------------|-------------------------------------------------------------------------------------------------------------------------------------------------------------------------------------------------------------------------------------------------------------------------------------------------------------------------------------------------------------------------------------------------------------------------------------------------------------------------------------------------------------------------------------------------------------------------------------------------------------------------------------------------------------------------------------------------------------------------------------------------------------------------------------------------------------------------------------------------------------------------------------------------------------------------------------------------------------------------------------------------------------------------------------------------------------------------------------------------------------------------------------------------------------------------------|
|                             | 
 
When the regulatory agency requires a suspension/complete termination of the trial and gives reasons for it.
 
                                                                                                                                                                                                                                                                                                                                                                                                                                                                                                                                                                                                                                                                                                                                                                                                                                                                                                                                                                                                                |
| Study Vaccine        | 
Study Vaccine: a COVID-19 Alpha/Beta/Delta/Omicron Variants S-Trimer Vaccine (SCTV01E);
 
Appearance: emulsified, white suspension (due to the presence of adjuvant);
 
Components:
 
 
Main active ingredients: TM22 protein (Alpha Variant), TM23 protein (Beta Variant), TM28 protein (Delta Variant), TM41 protein (Omicron Variant);
 
Adjuvant: SCT-VA02B;
 
Excipients: citric acid monohydrate, trisodium citrate dihydrate, sodium chloride, polysorbate 80;
 
 
Dosage form: solution for injection;
 
Strength: 30µg [5/5/5/15µg for TM22 (Alpha) /TM23 (Beta) /TM28 (Delta) /TM41 (Omicron)]/0.5mL/vial;
 
Route of vaccination: intramuscular injection into the lateral deltoid of the upper arm;
 
Dosage of vaccination: 30µg;
 
Immunization procedure: single dose;
 
Storage conditions: stored and transported at 2 ~ 8°C away from light;
 
Validity period: tentatively 24 months;
 
Manufacturer: Sinocelltech Ltd.
 
Control:
 
Normal saline will be used as placebo control in this study (0.5 mL/dose).
 |
| Statistical Analysis | 
The main statistical analysis methods in this study are described in this chapter, and details will be listed in the statistical analysis plan.
 
Hypothesis:
                                                                                                                                                                                                                                                                                                                                                                                                                                                                                                                                                                                                                                                                                                                                                                                                                                                                                                                                                                                       |

Define VE (vaccine efficacy) as  $1 - \text{hazard ratio (HR)}$ .

For the primary efficacy endpoint, the null hypothesis is

**H0:** The VE of SCTV01E versus control is  $\leq 30\%$ .

**H1:** The VE of SCTV01E versus control is  $> 30\%$ .

